**Design:**

TRUE HAVEN is an ongoing, multi-level intervention with three primary components: financial education paired with housing support (individual level), trauma-informed counseling (neighborhood level), and policy changes to address structural racism (city/state level). Six neighborhoods with among the highest rates of gun violence in New Haven, Connecticut, will receive the individual and neighborhood level intervention components sequentially beginning at staggered 6-month steps. Residents of these neighborhoods will be eligible to participate in the housing stability and financial education component if they were recently incarcerated or are family members of currently incarcerated people; participants will receive intense financial education and follow-up for six months and be eligible for special down payment and rental assistance programs. In addition, trusted community members and organization leaders within each target neighborhood will participate in trauma-informed care training sessions to then be able to recognize when their peers are suffering from trauma symptoms, to support these affected peers, and to destigmatize accessing professional mental health services and connect them to these services when needed. Finally, a multi-stakeholder coalition will be convened to address policies that act as barriers to housing stability or accessing mental healthcare. Interventions will be delivered through existing partnerships with community-based organizations and networks. The primary outcome is neighborhood rate of incident gun violence. To inform future implementation and optimize the intervention package as the study progresses, we will use the Learn As You Go approach to optimize and assess the effectiveness of the intervention package on the primary study outcome.

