#### Coalition to address structural racism

We will convene a coalition of diverse stakeholders quarterly to elicit and review barriers to achieving housing stability and accessing mental health supports for our participants and to actively and collectively work to address these barriers. This Steering Committee (SC) is inclusive of CAB Members and augments this group with additional leaders at the local, city, and state levels, such as city and state officials, local and regional philanthropy, local businesses, law enforcement, and physical and mental healthcare and other social service providers and leadership of coalitions representing these providers. The TRUE HAVEN SC is well-suited to both identify policy and programmatic barriers to achieving equitable access to stable housing and mental healthcare as well as to collaboratively find and enact solutions to address such barriers. The SC will meet quarterly, review data on ongoing study outcomes, review information on barriers that have arisen to housing stability and accessing mental healthcare, and will engage in facilitated processes to propose and enact plans to address those barriers. We will track the number of barriers identified and initiatives enacted to address them at the local, city, and state levels over time.

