### Statistical considerations

#### Justification of sample size

The primary aim of this study is to compare the intervention effect of TRUE HAVEN versus control on average yearly shooting victim rates. With an average of 10,295 residents per neighborhood per year, leading to approximately 432,390 person-steps of follow-up over 3.5 years, for a two-sided test between Poisson rates with a Type I error of 0.05, intra-cluster correlation coefficient (ICC) of 0.50 as currently estimated in these 6 neighborhoods of New Haven, and a baseline shooting rate of 6 shooting victims per 10,000 persons per step in the control period as currently observed on average in these New Haven neighborhoods, our study will have about 80% power to detect a 28% decrease or greater in the primary outcome, average neighborhood shooting rates, in relation to the full TRUE HAVEN intervention package [24, 36].

For individual-level outcomes of the housing assistance component, with approximately 1400 total participants (i.e., 233 participant individuals/families per neighborhood group) enrolled during the 3.5 year study period, that is, about 33 participants per neighborhood per 0.5 year step, for binary outcomes (e.g., % homeownership, % housing costs < 30% of income, % improved credit score), for a two-sided test of the difference between proportions with a Type 1 error of 0.05, with ICCs as low as 0.01 and as high as 0.2, our study will achieve at least 80% power to detect an increase with the TRUE HAVEN intervention of at least 2.4% points for outcomes where the baseline proportion is 1% or less, 10% points for outcomes where the baseline proportion is 20% or less, and 12% points for outcomes where the baseline proportion is 40% or less.

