### Limitations

First, the neighborhoods under intervention are geographically close to each other and social networks spanning across neighborhood are expected. Benefits received from the intervention among those in one neighborhood may affect those in another, which leads to the spillover of the treatment effect. Second, TRUE HAVEN is a non-blinded study due to practical considerations, and the sequenced time of initiation of the intervention across the neighborhoods are known. Although the primary outcome of gun violence incident rate is perhaps less at risk of bias from lack of blinding, certain secondary outcomes could result in bias due to non-blinding. Third, our study site is located in New Haven, CT, a northeast U.S. city, and has potentially limited generalizability to other locations where the causes of gun violence and the amount of community resources may be different. Fourth, there may be exogenous factors that affect rates of gun violence over the course of 5 years (e.g., changes in funding, elections of new political leaders) that make the results more difficult to interpret. We can use data from neighborhoods in similar Connecticut cities, Bridgeport and Hartford, that can serve as additional comparisons to identify secular trends.

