## Conclusion

TRUE HAVEN will generate data on the effect of a novel intervention package on reducing community gun violence. At this project’s completion, evidence for whether and how addressing structural racism citywide by increasing housing stability and home ownership, income and wealth, and access to mental health services will lead to a reduction in gun violence will be available.

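### exp(β1) estimates the stepped housing and trauma components given the citywide policy work, not the full three-component package to which the plan attributes it

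*Protocol article*

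**What the plan says.** All references are to the protocol article.

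- **Components.** The abstract (Design), the Introduction and the Discussion describe three components: housing with financial education, trauma-informed training, and policy change at city/state level.
- **What is stepped.** The abstract says the six neighborhoods "will receive the individual and neighborhood level intervention components sequentially beginning at staggered 6-month steps". Intervention overview likewise ties only housing enrollment and trauma training to a neighborhood's six-month period.
- **What is not stepped.** Under Coalition to address structural racism: "We will convene a coalition of diverse stakeholders quarterly to elicit and review barriers". Its remit is local, city and state, with no link to any neighborhood's step. Current status reports that the steering committee was already meeting quarterly while enrollment was open.
- **Model.** Statistical analyses specifies a log-Poisson model with one intervention indicator X_ij, step indicators for seven steps, a population offset and a neighborhood effect. It presents exp(β1) as the rate ratio for the intervention as a whole.
- **Power.** Justification of sample size says "our study will have about 80% power to detect a 28% decrease or greater in the primary outcome", and places that decrease "in relation to the full TRUE HAVEN intervention package".
- **Comparison and claim.** Objectives and hypotheses compares TRUE HAVEN with usual conditions. The abstract's Discussion promises evidence on whether citywide action on structural racism reduces gun violence. The Conclusion promises "evidence for whether and how addressing structural racism citywide by increasing housing stability", and goes on to name home ownership, income and wealth, and access to mental health services.

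**The concern.** A stepped-wedge model learns about an intervention from differences between neighborhoods that have and have not crossed over within the same step. A component that changes conditions for all six neighborhoods at once produces no such difference. To the extent that city or state policy change reaches neighborhoods not yet stepped, the cells coded X = 0 are not strictly under usual conditions, and the step indicators take up the shared change.

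At stake is the meaning of the headline number. A reader would take exp(β1) as the effect of all three components against no program, and as a verdict on citywide structural change. It is neither. A result near 1 could be read as failure of the package when it concerns only two of its components. A result below 1 could be credited to policy work that the analysis did not isolate.

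**Working it through.** **1. The plan's own figures.** The plan states "With an average of 10,295 residents per neighborhood per year, leading to approximately 432,390 person-steps of follow-up over 3.5 years". Check: 10,295 × 6 neighborhoods × 7 steps = 432,390, which agrees.

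For the 80%, the inputs are a control rate of 6 per 10,000 per step, ICC 0.50 and a two-sided 0.05 test. Assumptions: one neighborhood crosses per step from step 2 and stays treated (21 control and 21 treated cells); total variance equals the control rate and is split in half by the ICC; the z-test is on the rate difference.

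- Residual variance per cell: 0.0003 divided by 10,295, which is 2.914 × 10⁻⁸. The neighborhood variance (0.0003) is so much larger that the comparison is in effect within neighborhood.
- Without step effects, the information on X is the sum of k(7 − k)/7 for k from one to six, which is 8. The SE is the square root of 2.914 × 10⁻⁸ divided by 8, which is 6.04 × 10⁻⁵.
- The difference is 0.0006 × 0.28 = 1.68 × 10⁻⁴. Divided by the SE it is 2.78; subtracting 1.96 leaves 0.82, and Φ(0.82) gives power of about 79.5%. This reproduces the stated figure.
- With step effects, the information is 21, minus 13 (squared row totals, 91, over 7), minus 15.17 (squared column totals, 91, over 6), plus 10.5 (squared grand total, 441, over 42), which is 3.33. Power is then about 43.5%.

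The gap between 79.5% and 43.5% comes from adjusting for time. It is a separate matter and no part of this point.

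**2. Can the model see a shared citywide effect?** Write the mean model for the 42 cells as intercept, X_ij and six step indicators. This matrix has rank 8. Add a column for a citywide policy effect, switched on at any of steps 1 to 7 or rising linearly. The rank stays 8, so the new column is an exact combination of the intercept and step indicators.

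**3. What exp(β1) returns.** The planned mean model was fitted to exact expected counts:

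| Stepped RR | Shared citywide RR | Product | exp(β1) |
|---|---|---|---|
| 1.00 | 0.72 | 0.72 | 1.00 |
| 0.90 | 0.80 | 0.72 | 0.90 |
| 0.80 | 0.90 | 0.72 | 0.80 |

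exp(β1) equals the stepped rate ratio every time. It equals the package rate ratio only if the shared effect is null.

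**4. Policy that works through the stepped components.** Suppose the stepped RR is 0.90 and, from step 3, policy multiplies the rate by a further 0.80 in treated neighborhoods only, giving 0.72 there. The fit returns exp(β1) = 0.743. Most of this policy gain enters β1, because it differs between treated and untreated neighborhoods.

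**5. Size.** If 0.72 is meant as the full-package rate ratio, the target of β1 is 0.72 divided by the shared citywide RR. The splits are assumptions. Power is shown beside its own baseline so that the time-adjustment issue is not counted here.

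| Assumed citywide RR | Target of exp(β1) | Power, variant that reproduces 80% | Power, step effects added |
|---|---|---|---|
| 1.00 | 0.72 | 79.5% | 43.5% |
| 0.95 | 0.76 | 67% | 34% |
| 0.90 | 0.80 | 51% | 25% |
| 0.85 | 0.85 | 33% | 16% |
| 0.80 | 0.90 | 17% | 9% |

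**The case against.** The best case for the plan has four parts.

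- **Policy may act mainly through the stepped components.** The coalition reviews barriers facing participants, and Objectives and hypotheses says the policy work is also meant to facilitate the other two components. This stands in part: step 4 of the working shows such gains largely enter β1. It would be wrong to infer that the analysis is blind to policy altogether. The third component is nevertheless defined at city/state level, and whatever part is shared by all six neighborhoods remains unseen.
- **The word package is used loosely.** Overall design speaks of a package delivered sequentially, which fits the stepped bundle, and Statistical analyses refers to two key components. The Discussion uses the word for all three strategies, and the power text adds that it means the full package. The inconsistency is itself a reason to define the parameter.
- **The Conclusion lists mainly targets of the stepped components.** True, and β1 informs on much of that list. The citywide wording, broadest in the abstract's Discussion, still goes further than the primary analysis.
- **Other cities can be used.** Limitations mentions Bridgeport and Hartford data "that can serve as additional comparisons to identify secular trends". This is offered as an option, outside the primary model.

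Three stronger readings are tempting and not supported. A reader might infer that the randomized comparison is biased; a shared policy effect does not bias the contrast of the stepped components. A reader might infer that successful policy would shift the estimate; a shared effect leaves exp(β1) unchanged, and the gap arises only if 0.72 was meant as the three-component total. A reader might also blame this point for all the low power in the last column of the working; much of it comes from the step adjustment.

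**Conclusion.** The point holds as a wrongly labelled primary parameter. exp(β1) is the rate ratio for the stepped housing/financial and trauma components given the concurrent citywide policy activity, including policy gains that act only through those components in treated neighborhoods. It is not the effect of the whole intervention against usual conditions.

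That a shared effect is absorbed follows exactly from the step indicators. The working's crossover pattern, one neighborhood per step and staying treated, is assumed. The size is unknown because the documents give no split between components. Over the assumed range of shared citywide rate ratios from 0.95 to 0.80, a full-package 0.72 becomes a target of 0.76 to 0.90. If the policy work has no effect shared across neighborhoods, the numerical gap vanishes, but the plan gives no ground for assuming that.

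**What to change.** 1. In Justification of sample size and Statistical analyses, define exp(β1) as the effect of the stepped components given the concurrent citywide policy activity, and remove the wording that makes it the effect of the full or overall intervention.
2. State that the 28% detectable decrease refers to the stepped components.
3. In the abstract's Discussion and in the Conclusion, do not say that the primary analysis shows the effect of the policy component or of addressing structural racism citywide.
4. If the citywide claim is kept, pre-specify a secondary comparison with the Bridgeport and Hartford neighborhoods that Limitations says can be used. Label it non-randomized, and note that state-level changes also reach those cities. The article gives no onset date for policy change, so this comparison would be weaker evidence than the stepped contrast.

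Items 1 to 3 cost only wording: randomization, data collection and the primary model stay as they are. Item 4 needs external data and arises only if the claim is retained. The downside is a narrower headline claim.

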### Objectives and hypotheses

Among communities with well-being damaged by gun violence, our study aims to compare effectiveness of TRUE HAVEN vs. conditions as usual on the incidence of gun violence at the neighborhood level. We hypothesize TRUE HAVEN will be associated with lower incident gun violence compared with conditions as usual. Second, we will compare the effect of TRUE HAVEN vs. conditions as usual on secondary outcomes including social cohesion of the neighborhood, and among participants enrolled in the housing stability component, changes in their self-efficacy, perceived health and well-being, and financial security. We hypothesize that the intervention will lead to improvement in these outcomes. Lastly, for each intervention component, we hypothesize the following: (1) pairing rigorous financial education with financial support for home ownership and rental assistance will increase families’ housing stability and neighborhood cohesion, changing the neighborhood context and decreasing gun violence; (2) training trusted community members in trauma-informed counseling will provide needed psychosocial support for families and communities affected by gun violence, heighten awareness of community members affected by trauma, destigmatize accessing mental healthcare, and improve access to mental healthcare, thereby breaking the cycle of trauma and violence; and (3) convening a coalition of decision-makers and influencers at the city and state level to address structural and policy barriers that prohibit achieving housing stability and accessing mental healthcare, thereby actively dismantling structurally racist policies and facilitate components (1) and (2).

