## Methods

### Overall design

The purpose of TRUE HAVEN is to assess the feasibility of implementing a city-wide intervention to address structural racism, and if so, to evaluate the extent to which it reduces the incidence and effects of community gun violence and creates the enabling conditions for historically marginalized populations to thrive. Funded by the National Institute on Minority Health and Health Disparities (NIMHD), TRUE HAVEN is a hybrid type 1 effectiveness-implementation stepped wedge trial [22–24] enrolling participants living in one of six participating neighborhoods (see Fig. 1). The staggered roll-out of the stepped wedge designs is useful for rolling out and maintaining complex multi-level community-based interventions, and addresses potential ethical concerns since all units receive the intervention by the end of the trial. TRUE HAVEN implements a 6-month intervention package sequentially across six neighborhoods of New Haven with high rates of gun violence and evaluates the intervention’s impact over extended follow-up periods (see Table 1 for the timeline).

**Table 1 Tab1:** Timeline of TRUE HAVEN and list of activities by year and 6-month period

	Year 1		Year 2		Year 3		Year 4		Year 5	
**Activity**	1–6	7–12	13–18	19–24	25–30	31–36	37–42	43–48	49–54	55–60
Preparing, planning, piloting, and optimizing										
Research team meetings	**•**	**•**	**•**	**•**	**•**	**•**	**•**	**•**	**•**	**•**
Hire/train research staff; IRB approval	**•**									
Convene CAB, plan and pilot interventions	**•**									
Optimize interventions; weekly data review and adaptation		**•**								
Implementation and evaluation										
Recruit families affected by incarceration, with 2 new neighborhoods randomly eligible each year (stepped wedge)			**•**	**•**	**•**	**•**	**•**	**•**		
Rapid qualitative and quantitative data collection (e.g., ROMA, interviews of clients/staff)	**•**	**•**	**•**	**•**	**•**	**•**	**•**	**•**	**•**	**•**
CAB meets monthly to review data, evaluate progress, and adapt		**•**	**•**	**•**	**•**	**•**	**•**	**•**	**•**	**•**
DSMB meets bi-annually to review data and safety		**•**		**•**		**•**		**•**		**•**
Assess Final Intervention Outcomes and Disseminate										
Overall evaluation of effectiveness on study outcomes							**•**	**•**	**•**	**•**
Cost-effectiveness analyses									**•**	**•**
Use simulation to develop partnerships to plan for sustainability		**•**		**•**		**•**		**•**	**•**	**•**

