### Intervention overview

Our community-academic team designed TRUE HAVEN, a community-based intervention that acts on two leverage points in our community’s systems that are most feasibly intervened upon and projected to be most impactful: (1) housing stability (for recently incarcerated individuals as well as family members of incarcerated people) and (2) mental well-being. We will study the effect of our intervention using a cluster-randomized, stepped-wedge study design. Each of six neighborhood’s residents will be eligible for enrollment in the housing stability component of the initiative for a 6-month period and during this time, trusted community members in this neighborhood will be trained in trauma-informed counseling. In addition, TRUE HAVEN will employ the Learn As You Go (LAGO) approach [27] that analyzes intervention implementation and outcome data at each trial stage to tweak and tailor the intervention as the trial progresses to optimize the cost-effectiveness of the package, mitigating the risk of an intervention failure. LAGO will provide rich contextual and experiential data for our evaluation of the intervention package.

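### The power statement for individual-level housing outcomes assumes participants in control steps, but residents enroll only when their own neighborhood opens, so the stated 80% power does not describe the actual design

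*Protocol article*

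**What the plan says.** **Power (Justification of sample size).** The calculation takes "approximately 1400 total participants (i.e., 233 participant individuals/families per neighborhood group"), "enrolled during the 3.5 year study period", and converts this to "about 33 participants per neighborhood per 0.5 year step". It is stated "for a two-sided test of the difference between proportions with a Type 1 error of 0.05", with ICCs from 0.01 to 0.2. The claim is that "our study will achieve at least 80% power to detect an increase" of 2.4, 10 and 12 percentage points from baselines of 1%, 20% and 40%. The example outcomes are homeownership, housing costs below 30% of income, and improved credit score.

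**Enrollment.** Under Intervention overview, each neighborhood's residents "will be eligible for enrollment in the housing stability component of the initiative for a 6-month period", and the trauma training runs in the same period. Table 1 (Overall design) schedules recruitment in months 13 to 48, "with 2 new neighborhoods randomly eligible each year (stepped wedge"). The abstract's Design paragraph starts the individual-level component at each neighborhood's own step. Under Recruitment, procedures, and follow-up, enrollees are assessed at baseline on the day they enroll, then enter the financial education program, and are contacted again at 6 months, 1 year and 2 years.

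**Comparison and analysis.** Objectives and hypotheses says "we will compare the effect of TRUE HAVEN vs. conditions as usual on secondary outcomes". For housing participants, that sentence goes on to name changes in self-efficacy, perceived health and well-being, and financial security. Statistical analyses carries the general approach of the primary model, which contains step indicators, over to these outcomes and adds a random effect for repeated measures.

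**The concern.** A stepped-wedge power calculation with an equal number of new people in every cell needs people who are recruited and measured while their neighborhood is still under usual conditions. The article describes no such recruitment. Each participant enters in the neighborhood's own open window and is under intervention from then on.

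Two things are at stake. First, the 80% figure and the three detectable differences are attached to a contrast that the trial will not observe, so readers cannot use them to judge the precision of the housing results. Second, a result labeled as an effect against conditions as usual would in fact be change after enrollment among people who chose to join. For an outcome that exists only after enrollment, it would have no untreated counterpart at all.

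**Working it through.** **1. Cell size.** 1,400 / 6 = 233 per neighborhood; 233 / 7 = 33 per neighborhood-step. There are 6 × 7 = 42 cells.

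**2. Control cells.** Assume one neighborhood crosses over at each step after the first. This is inferred from 6 neighborhoods, 7 steps and six-month staggering. The control steps are then 1 + 2 + 3 + 4 + 5 + 6 = 21 of 42. At 33 per cell, that is 21 × 33 = 693 of 1,386 people, or about 700 of 1,400.

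**3. Reproducing the stated figures.** The standard cross-sectional stepped-wedge variance (Hussey and Hughes), with step effects and a random neighborhood intercept, is

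Var = Iσ²(σ² + Tτ²) / [(IU − W)σ² + (U² + ITU − TW − IV)τ²]

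Here I = 6, T = 7, U = 21, W = 91 (sum of squared column totals of the treatment matrix) and V = 91 (sum of squared row totals). So IU − W = 35, and U² + ITU − TW − IV = 441 + 882 − 637 − 546 = 140. With baseline variance, σ² = (1 − ICC)p₀(1 − p₀)/33 and τ² = ICC·p₀(1 − p₀).

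Example, 20% to 30% at ICC 0.01:
- σ² = 0.99 × 0.16 / 33 = 0.0048; τ² = 0.0016.
- Var = 6 × 0.0048 × (0.0048 + 0.0112) / (35 × 0.0048 + 140 × 0.0016) = 0.0004608 / 0.392 = 0.001176.
- SE = 0.0343, and power = Φ(0.10/0.0343 − 1.96) = Φ(0.957) = 83.1%.

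| Contrast | Power, ICC 0.01 | Power, ICC 0.2 | Detectable at 80%, ICC 0.01 |
|---|---|---|---|
| 1% + 2.4 points | 80.3% | 81.2% | 2.39 points |
| 20% + 10 points | 83.1% | 83.9% | 9.61 points |
| 40% + 12 points | 81.5% | 82.4% | 11.76 points |

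The last column rounds to the stated 2.4, 10 and 12. Other variants were tried: variance at the average or the intervention proportion, no step effects, a different ICC convention, and a simple two-sample test with or without a design effect. None returned all three. The published figures therefore very probably rest on filled control cells.

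**4. The enrollment that is described.** Residents enter only in their own six-month window, so the pattern is about 233 people in one step per neighborhood. The 21 control cells hold 0 new participants instead of 693.

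**5. What can be estimated.**
- *Post-enrollment values only.* The intervention indicator equals 1 for every observation and so equals the sum of the step indicators (rank 6 for 7 non-empty columns). No effect against usual conditions is estimable. Improved credit score is in this position, because improvement has no value on the day of enrollment.
- *Baselines included as untreated values.* Place 233 enrollees per neighborhood in their own step, with the baseline untreated, follow-up 1, 2 and 4 steps later, and data cut off at step 7. The design then has full rank (7 of 7). The model has step effects, a random neighborhood intercept and baseline variance. Within-person correlation is not in the article; 0 and 0.5 were assumed. For the 20% baseline, the standard error is 1.3 to 2.0 points across ICC 0.01, 0.05 and 0.2. Power for all three stated differences exceeds 99%.

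**The case against.** The best defense is that the housing outcomes do have untreated data. Every participant has a baseline, baselines in later-opening neighborhoods are concurrent with follow-up in earlier ones, the model already has step effects, and the objective already speaks of changes among enrollees. Under simple assumptions the contrast built on those baselines has more power than the article claims.

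This stands, and it limits the point. A reader might infer that these outcomes have no controls at all, or that secular change is ignored. The documents do not support either reading for outcomes with an enrollment value. A reader might also infer bias from regression to the mean, but eligibility rests on residence and incarceration history, not on outcome values, so that is unproven.

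The defense does not rescue the power sentence, which describes new people in every cell and not repeated measures on enrollees. Nor does it help an outcome without a baseline.

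Two further limits are fair. Homeownership is listed in Table 2 as neighborhood-level data from the state housing finance authority, which could cover control steps, although the power paragraph treats it as an individual-level outcome. And the flow, schematic and schedule figures are not shown, so the 21/21 split is an inference. That participants are absent from control steps follows from the enrollment text whatever the exact split.

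**Conclusion.** The point holds as a wrong stated figure and a mislabeled comparison on secondary, participant-level outcomes. About 700 of the 1,400 people in the calculation would sit in control steps where the described enrollment places none. The 80% power therefore does not describe this trial, and outcomes with no enrollment value support no comparison with usual conditions.

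It does not follow that the trial is underpowered for participant change. The figure above 99% shows only that the effect is identified. It assumes no attrition, a neighborhood effect that is constant over time and fully weighted estimation, and should not replace the published number as it stands. That contrast is also not randomized at the person level.

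It may be tempting to add that the reconstructed formula dips to 76% to 79% at ICC 0.05, or to 48% for the 1% baseline with average variance. The article names no formula or variance convention, so these are side points about a reconstruction and not part of the finding.

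The primary outcome uses police data available in every neighborhood-step and is unaffected, as are outcomes taken from neighborhood-level administrative data. This should be fixed, but it does not threaten the main result.

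**What to change.** 1. Reconcile Justification of sample size with Intervention overview. If people are to be recruited and measured in control steps, say how; otherwise drop the 33-per-cell power statement.
2. For participant-level outcomes with an enrollment value, define the target as within-participant change from enrollment. Keep the calendar-step effects already in the model, so that baselines in later-opening neighborhoods serve as concurrent untreated values.
3. Replace the power sentence with the expected precision of that contrast in about 1,400 people, stating the assumed within-person correlation, attrition and ICC.
4. Report outcomes without an enrollment value, such as improved credit score, descriptively and not as an effect against conditions as usual.
5. State whether homeownership is analyzed from participants or from neighborhood-level administrative data.

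The cost is revised wording in the objectives, sample-size and analysis sections and one recalculation. No new data are needed. The claim for the participant outcomes becomes more modest.

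### The detectable increases stated for the housing component's binary outcomes do not carry the claimed 80% power: 2.4 points at a 1% baseline has about 41-56%, and the 10- and 12-point figures fall short by less

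*Protocol article*

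**What the plan says.** The second paragraph of Justification of sample size covers binary outcomes of the housing component. It assumes about 1,400 participants, 233 per neighborhood, or "about 33 participants per neighborhood per 0.5 year step". The calculation is described as being "for a two-sided test of the difference between proportions with a Type 1 error of 0.05". The ICC is not fixed at one value; the claim is made "with ICCs as low as 0.01 and as high as 0.2". On that basis the article says that "our study will achieve at least 80% power to detect an increase with the TRUE HAVEN intervention". The sizes given are "2.4% points for outcomes where the baseline proportion is 1% or less, 10% points for outcomes where the baseline proportion is 20% or less"; a third size, 12 points, is tied to a baseline of 40% or less.

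The paragraph does not say which variance was used or whether step effects were included. Statistical analyses specifies a model for the primary outcome with an effect for each step, over six neighborhoods and seven steps. It says the same general approach will be used for outcomes of the individual components.

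**The concern.** A rise from 1% to 3.4% more than triples the binomial variance: 0.034 × 0.966 / (0.01 × 0.99) = 0.03284 / 0.0099 = 3.3. A formula that carries the 1% variance into the intervention cells will overstate power badly for rare outcomes and slightly for common ones. In addition, power in a stepped-wedge layout need not fall or rise steadily with the ICC. A claim covering a whole ICC range therefore has to be checked inside the range as well as at its ends.

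What is at stake is how a null result is read. If an outcome with a baseline near 1% shows no significant change, readers will take the promised 80% power as a reason to believe there was no increase of 2.4 points. With power near one half, that inference fails.

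**Working it through.** **Inputs.** From Justification of sample size: two-sided α = 0.05, n = 33 per cell, ICC ρ from 0.01 to 0.2, and increases 1%→3.4%, 20%→30% and 40%→52%. From Statistical analyses: I = 6 neighborhoods, T = 7 steps, step effects in the model. Assumption: all neighborhoods start in control and one crosses over per step, giving 21 control and 21 intervention cells. Total 6 × 7 × 33 = 1,386, which agrees with about 1,400.

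**Formula** (Hussey-Hughes, fixed step effects). With σ² = v(1−ρ)/n and τ² = vρ, where v is the binomial variance:

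Var = Iσ²(σ² + Tτ²) / [(IU−W)σ² + (U² + ITU − TW − IV)τ²]

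Here U = 21 and W = V = 91, so IU−W = 35 and the τ² coefficient is 441 + 882 − 637 − 546 = 140.

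The standard error is g(ρ)√v. At ρ = 0.01, σ²/v = 0.03 and τ²/v = 0.01, so g² = 6(0.03)(0.10)/(1.05 + 1.40) = 0.00735 and g = 0.0857. In the same way g = 0.0904 at ρ = 0.05 and 0.0847 at ρ = 0.2. Power = Φ(d/SE − 1.96).

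**Step 1: the protocol's figures, using v = p0(1−p0) in every cell.** Example: √0.0099 × 0.0857 = 0.00853, 0.024/0.00853 = 2.81, Φ(0.85) = 80.3%.

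| ICC | 2.4 points at 1% | 10 points at 20% | 12 points at 40% |
|---|---|---|---|
| 0.01 | 80.3% | 83.1% | 81.5% |
| 0.05 | 76.1% | 79.0% | 77.3% |
| 0.2 | 81.2% | 83.9% | 82.4% |

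The differences with 80% power at the two end ICCs are 2.39/2.36, 9.6/9.5 and 11.8/11.6 points, close to the stated 2.4, 10 and 12. Even this favourable shortcut misses 80% at ICC 0.05.

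**Step 2: variance of both proportions, averaged.** v = (0.0099 + 0.0328)/2 = 0.0214, (0.16 + 0.21)/2 = 0.185, and (0.24 + 0.2496)/2 = 0.2448.

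| ICC | 2.4 points at 1% | 10 points at 20% | 12 points at 40% |
|---|---|---|---|
| 0.01 | 48% | 77% | 81% |
| 0.05 | 44% | 73% | 77% |
| 0.2 | 49% | 78% | 82% |

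Generalised least squares with arm-specific residual variances gives about 50-56%, 73-79% and 77-82%.

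**Step 3: the other reading of the ICC.** If the binomial variance is taken as the residual and τ² = vρ/(1−ρ), every variance above is divided by (1−ρ). With averaged variance at ICC 0.01 / 0.05 / 0.2, power is 48/43/41%, 77/71/69% and 80/74/73%.

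**Step 4: differences with 80% power.** Solve d = (1.960 + 0.842) g √v(d) at ρ = 0.05 with averaged variance.
- 1% baseline: d = 0.0443 gives v = 0.0306, and 2.802 × 0.0904 × 0.175 = 0.0443, so 4.4 points.
- 20% baseline: 10.95 points.
- 40% baseline: 12.5 points.

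Midpoint variance gives about 4.5, 11.0 and 12.6 at this ICC. Arm-specific variance gives about 3.7, 10.9 and 12.5. Over the whole ICC range and these variance forms, the 1% figure runs from roughly 3.4 to 4.5 points. The Step 3 reading raises all three somewhat.

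**Step 5: simulation.** The normal approximation is rough with 33 × 0.01 = 0.33 expected events per control cell. Simulated binomial data, analysed with fixed neighborhood and step effects, gave at ICC 0.01 / 0.05 / 0.2: 41/44/52% for 2.4 points, 69/71/78% for 10, and 73/74/81% for 12.

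**The case against.** The strongest reply is that the article states no formula. If step effects are left out and both variances are used, 2.4 points at 1% reaches roughly 76-87% power depending on the variance form, and 10 and 12 points reach about 97-99%. On the more favourable of those forms, all three literally satisfy the claim. This stands to one extent: a reader might infer that the control-only variance was certainly used, and the documents do not establish that. The reply does not rescue the sentence, because the planned model has step effects, and increases with 97-99% power would not have been chosen as the limits for 80%.

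The 10- and 12-point gaps are small. At both end ICCs the 12-point figure keeps 81-82% under the total-variance reading, and the difference needed is about 12.5 against 12. That is right, and these figures should not be put on a level with the 2.4-point error.

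A reader might also infer that power is always worst at an ICC of 0.05. That depends on how the ICC is defined. Under the second reading (Step 3) power falls steadily to 0.2.

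Nor do the documents show that a named outcome has close to even odds of detection. They give no baseline near 1% for homeownership, housing cost or credit score. Those are effectiveness outcomes in Table 2 (homeownership is listed there at neighborhood level), and none is in the Secondary outcomes section.

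The wording of 1% or less does not help. From 0.1% to 2.5%, midpoint variance gives 65-71%.

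**Conclusion.** Wrong as written. Under the planned step effects and the variance of both proportions, the 2.4-point claim at a 1% baseline has about 41-56% power in place of at least 80%. The 10-point claim has about 69-79%. The 12-point claim falls modestly short, to about 73-77%, at some ICCs within the stated range and is roughly met at others. Different ways of splitting the variance move these figures by a few points, and none brings the 2.4-point claim near 80%.

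The result assumes 33 observations in every cell, one crossover per step, an exchangeable ICC and no dropout. Allowing for dropout, or making a small-sample correction for six clusters, would lower power further. That the control-only variance is the source remains an inference. The point concerns effectiveness outcomes of the housing component. It does not touch the primary outcome or its power statement.

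**What to change.** Recompute the detectable differences with the variance at both the control and intervention proportions, the planned step effects, the least favourable ICC in the stated range, and the number of observations actually expected in each neighborhood-step. Name the formula and the ICC definition. Then restate the differences, or keep 2.4, 10 and 12 points and report the lower power.

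Under the layout as stated, the differences would be about 3.7-4.5, 11 and 12.5 points, or slightly more if the ICC is defined relative to the residual variance. Treat these as illustrative. Participants are assessed repeatedly, and enrolment opens neighborhood by neighborhood, so 33 observations in every control and intervention cell may not describe the real data.

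The cost is wording and a less favourable stated figure. No change to design or sample size follows from this point alone.
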